## 9.4 Statistical analysis

Once all subjects have completed the half-year follow-up (Visit F-U) and after any necessary settlement of queries etc. in the CRFs, data from all patients and visits will be locked. A full

analysis of the data available will be performed and a final clinical study report prepared. Results of the PRNT assay will be presented in an addendum to the clinical study report. For preparation of safety data as part of a potential Emergency Use Authorization (EUA) data package, a safety analysis will be performed on the population (MFAS) described in section 9.3 ('Study cohorts/data sets to be evaluated').

#### **9.4.1 Analysis of demographics and baseline characteristics**

The results will be compared descriptively (shown in a table). If large differences become apparent then a test will be done to check the significance.

#### **9.4.2 Analysis of Immunogenicity**

Antibody titers and resulting seroconversion rates will be assessed by direct ELISA and PRNT method as described in section 7.2.

The primary immunogenicity endpoint is the MVA-specific seroconversion rate derived from the ELISA specific antibody titers.

The primary hypothesis is to show that the humoral immune response of the study group with atopic dermatitis (Group 2) is not statistically inferior compared to the study group of healthy subjects (Group 1).

The above hypothesis will be tested based on an exact, unconditional test for binomial differences. In addition an exact one-sided 97.5% unconditional confidence interval for the difference of proportions will be calculated. If the lower limit of this confidence interval is greater than 5% (or equivalent the p-value of the non-inferiority test is less than 5%) then the null hypothesis will be rejected (StatXact®, Chan (1998), Agresti and Min (2001)).

In a first step, the primary null hypothesis as stated in section 9.1 will be tested 2 weeks after the last vaccination.

Secondary analysis will be done with the timepoints of Visit 2, Visit 3, Visit 5 and F-U and with the neutralization assay specific seroconversion rates (from PRNT) as above.

Descriptive statistics for Enzyme-Linked Immunospot (ELISPOT) will be provided.

T-cell samples will be analyzed if samples are available for the subject from Visit 1 and at least one of Visit 2 or Visit 4.

Summary tables will be provided for the FAS and the EAS.

All statistical tests for secondary time points and comparisons are regarded descriptive. No adjustment for multiple testing will therefore be done.

Seroconversion rates for each group at all visits will be tabulated and presented graphically by means of bar charts.

Tables showing geometric mean titer (GMT) with 95% confidence limits for each group at all blood sampling time points will be prepared. Additionally, the distribution of antibody titers will be displayed graphically by means of reverse cumulative curves.

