Suppose  $p_1$  is the seroconversion rate in healthy subjects (group 1) and  $p_2$  is the seroconversion rate in the subjects with atopic dermatitis (group 2).

The test on non-inferiority will be applied for the following hypothesis:

$$H_0: p_2 - p_1 \leq -\Delta \quad \text{versus} \quad H_1: p_2 - p_1 > -\Delta, \text{ where}$$

$\Delta$  is the non-inferiority margin and is chosen in this trial as 5%.

From the experience in the pilot trial POX-MVA-007 in subjects with atopic dermatitis subjects, it is anticipated that the seroconversion rate in both groups reaches at least 99%.

Assuming a significance level of 5%, a power of >80%, expected seroconversion rates of 99% in both groups, this yields to a sample size of 124 per group (248 in total). In order to account for about 5% drop out rate, a total of 130 subjects per group (260 in total) will be treated.

For the statistical consideration of the protocol extension, please refer to Appendix IV.

---

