### 9.1 Sample size calculation

The sample size calculation is based on the primary immunogenicity endpoint '**MVA-specific seroconversion rate**'.

The primary hypothesis is to show that the humoral immune response of the group with diagnosed atopic dermatitis (Group 2) is not statistically inferior compared to the group with healthy subjects (Group 1) at 10-14 days after the second vaccination (Visit 4). The study should demonstrate that the Group 2 seroconversion rate is not worse than the Group 1 seroconversion rate by more than a pre-specified amount. This amount is called the non-inferiority margin ( $\Delta$ ).

Suppose  $p_1$  is the seroconversion rate in healthy subjects (group 1) and  $p_2$  is the seroconversion rate in the subjects with atopic dermatitis (group 2).

The test on non-inferiority will be applied for the following hypothesis:

$$H_0: p_2 - p_1 \leq -\Delta \quad \text{versus} \quad H_1: p_2 - p_1 > -\Delta, \text{ where}$$

$\Delta$  is the non-inferiority margin and is chosen in this trial as 5%.

From the experience in the pilot trial POX-MVA-007 in subjects with atopic dermatitis subjects, it is anticipated that the seroconversion rate in both groups reaches at least 99%.

The above hypothesis will be tested based on an exact, unconditional test for binomial differences. In addition an exact one-sided 97.5% unconditional confidence interval for the difference of proportions will be calculated. If the lower limit of this confidence interval is greater than  $\tilde{\alpha}$  5% (or equivalent the p-value of the non-inferiority test is less than 5%) then the null hypothesis will be rejected (StatXact®, Chan 1998, Agresti and Min 2001).

Assuming a significance level of 5%, a power of > 80%, expected seroconversion rates of 99% in both groups, this yields to a sample size of 124 per group (248 in total). In order to account for drop outs, a total of 130 subjects per group (260 in total) will be treated.

For the statistical consideration of the protocol extension, please refer to Appendix IV.

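### The primary non-inferiority rule treats a one-sided 97.5% confidence limit and a p-value below 5% as the same criterion, but they are tests at 2.5% and 5%.

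*Protocol*

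**What the plan says.** The hypothesis in Protocol section 9.1 is one-sided, with null "H_0: p_2 - p_1 \leq -\Delta", and Δ "is the non-inferiority margin and is chosen in this trial as 5" per cent. The test is an exact unconditional test for a difference of binomial proportions. In addition, "an exact one-sided 97.5% unconditional confidence interval for the difference of proportions will be calculated".

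Section 9.4.2 then gives the decision rule: "If the lower limit of this confidence interval is greater than 5% (or equivalent the p-value of the non-inferiority test is less than 5" per cent). Section 9.1 carries the same rule with the same parenthesis.

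The sample-size paragraph of 9.1 reads "Assuming a significance level of 5%, a power of > 80%, expected seroconversion rates of 99% in both groups", leading to 124 per group. The synopsis repeats it: "Assuming a significance level of 5%, a power of >80%, expected seroconversion rates of 99% in both groups". Neither says whether the 5% is one-sided or two-sided. The synopsis has no confidence-limit or p-value decision rule, so it carries only the missing sidedness.

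**The concern.** A confidence limit and a p-value give the same decision only when their levels match. For this one-sided hypothesis, a one-sided 97.5% lower limit above the margin is the test at one-sided 2.5%. A non-inferiority p-value below 5% is the test at one-sided 5%, whose matching limit is one-sided 95%. The protocol joins the two as if either could be used.

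This is the trial's primary decision, and section 9.3 bases all confirmatory testing on the per-protocol set. Outcomes that meet the limit criterion also meet p<5%, so a rule that accepts either is in effect a 5% rule. If the choice is left until the data are seen, the error rate of the claim is not fixed in advance. Section 9.4.2 also applies the method to the secondary time points and PRNT, though only descriptively. Appendix V refers the evaluation of healthy subjects on the new lot to section 9.

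**Working it through.** **Inputs.** From section 9.1: margin 5 points, 99% seroconversion in both groups, power above 80%, exact unconditional test, 124 per group. From the synopsis: about 5% drop-out. From Appendix V: 230 healthy and 330 AD subjects in the enlarged trial.

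**1. Matching levels.** A one-sided limit with confidence 1 - α pairs with one-sided p < α. So 97.5% pairs with p < 0.025, and p < 0.05 pairs with 95%.

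**2. Reproducing 124.** The simple normal formula is n = (z_α + z_0.80)² × 2 × 0.99 × 0.01 / 0.05².
- One-sided 2.5%: (1.960 + 0.842)² × 7.92 = 62.2, so 63.
- One-sided 5%: (1.645 + 0.842)² × 7.92 = 49.0, so 49.

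Neither gives 124, so the plan's figure did not come from this formula. An exact unconditional test, with outcomes ordered by the score statistic (Farrington-Manning) and size maximised over the nuisance rate, gives at 99%/99%:

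| n per group | Power, one-sided 2.5% | Power, one-sided 5% |
|---|---|---|
| 103 | 61.1% | 78.3% |
| 104 | 60.9% | 85.1% |
| 123 | 74.1% | 84.2% |
| 124 | 73.9% | 90.8% |
| 125 | 81.8% | 90.6% |
| 130 | 81.0% | 90.0% |

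Exact power moves in a saw-tooth. At one-sided 2.5% it first exceeds 80% at 125. At one-sided 5% it first does so at 93 and stays above from 104. The step from 124 to 125 turns on a single outcome, 1 healthy and 2 AD non-responders, which has p = 0.0256 at 124. So 124 against 125 is a match within the tolerance of ordering and software.

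**3. Type I error at 124 per group.** The maximum is 0.0246 under the 97.5% limit and 0.0498 under p<5%.

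**4. An outcome on which the criteria split.** Take 124 per group, 0 healthy and 2 AD non-responders. This one can be checked by hand at the null boundary p1 = 1, p2 = 0.95, where the p-value is the probability of at most 2 AD non-responders:

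0.95^124 + 124 × 0.05 × 0.95^123 + 7626 × 0.05² × 0.95^122 = 0.0017 + 0.0113 + 0.0365 = 0.0495.

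The full maximisation returns the same 0.0495. It is below 5% and above 2.5%: success on the p-value, failure on the limit. With all 124 healthy subjects responding, p<5% accepts 122 AD responders and the limit requires 123. At 99%/99% the two criteria disagree in 90.8% - 73.9% = about 17% of trials of this size.

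**5. The enlarged sample.** Assume 5% loss applies to both groups: 230 × 0.95 = 218.5 and 330 × 0.95 = 313.5, taken as 218 and 313.

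| True rates, healthy/AD | Success, one-sided 2.5% | Success, one-sided 5% |
|---|---|---|
| 99% / 99% | 99.8% | >99.9% |
| 99% / 98% | 89.5% | 95.9% |
| 99% / 97% | 56.0% | 73.0% |

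Split outcomes still exist: 0 healthy and 9 AD non-responders gives p = 0.047. That is about three times the AD failures expected under the planning rate (313 × 1% = 3.1).

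**The case against.** The best defence is that 5% means two-sided 5%, a common convention and exactly equal to one-sided 2.5%. On that reading the sample-size sentences agree with the interval and only lack a word. This is plausible, but the documents do not say it. The p-value is named as that of the non-inferiority test, whose hypotheses are one-sided, so an analyst who follows the parenthesis literally tests at double the level of the interval.

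It is also fair that the effect on power is small where the plan expects to be: at 99%/99% with the enlarged sample, success is near certain under either rule. The larger gaps need an AD rate of 98% or 97%, which the protocol does not assume, or the original 124 per group, which the extension supersedes.

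Two stronger readings are tempting, and the documents support neither.

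- **A threshold of +5%.** Section 9.4.2 prints the comparator without a sign, and a reader might infer a rule that could hardly ever be met. But the hypotheses fix -5%, section 9.1 shows a damaged character where the minus belongs ("If the lower limit of this confidence interval is greater than $\tilde{\alpha}$ 5" per cent), and 9.4.2 refers back to the null hypothesis in 9.1. A lost minus sign is the likely explanation. It has no part in the conflict between 2.5% and 5%.
- **124 proves that 2.5% was meant, or that the trial was undersized.** At 124 the calculation here gives 73.9% at one-sided 2.5%, short of the stated 80%, and 90.8% at one-sided 5%. Restricting the healthy non-response rate to at most 12% in the maximisation raises the 2.5% figure at 124 to 82%. The result depends on method, so it shows neither proof of intent nor a sample-size error.

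**Conclusion.** The point holds. Sections 9.1 and 9.4.2 equate two criteria with different maximum type I errors, about 2.5% and about 5%, and the two can give opposite answers on the same data. The conflict disappears only if the 5% p-value is two-sided, which the protocol does not state.

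The size of the planned sample favours one-sided 2.5%: 124 is one subject per group from the computed 125, and about 20 above the 104 needed at one-sided 5%. That is support and no more. The consequence is mainly the error rate of the confirmatory claim; power at the planning rates is barely touched. The figures rest on score ordering and full maximisation over the nuisance rate, and those for the enlarged sample also on an assumed 5% loss in each group.

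**What to change.** - In sections 9.1 and 9.4.2, state one rule: the null is rejected when the exact one-sided 97.5% lower limit for p2 - p1 lies above -5%, which is the same as one-sided p < 0.025 when limit and p-value come from the same exact procedure.
- In section 9.1 and the synopsis, replace the unqualified 5% level with one-sided 2.5% (two-sided 5%).
- Restate power at that level for the enlarged sample. On the assumptions above it is about 99.8% at 99%/99% and about 90% at 99%/98%.
- Print the minus sign before 5% in both sections, as an editorial correction.

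The cost is a wording change in three places and a restated power figure. No subjects, visits or assays are affected. It should be settled before the primary data are analysed.

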#### **9.4.3 Analysis of safety and reactogenicity**

##### Solicited local adverse events

The occurrence of solicited local adverse events within 1 week after each vaccination will be summarized on a per patient and per vaccination basis.

The maximum intensity over the 7-day period after vaccination will be used and categorized as follows:

Pain: Grade > 0

Grade ≥ 2

Grade ≥ 3

For measurements of diameter size: Diameter > 0 mm

Diameter ≥ 30 mm

Diameter ≥ 100 mm

These categories will be compared between treatment groups by means of the exact test of Fisher (or its normal approximation, the chi-squared test).

#### Solicited systemic adverse events

Occurrence of solicited systemic adverse events within 1 week after each vaccination will be summarized per patient and vaccination.

The maximum intensity over the 7-day period after vaccination will be used and categorized as follows:

Grade > 0

Grade ≥ 2

Grade ≥ 3

These categories will be compared between treatment groups by means of the exact test of Fisher (or its normal approximation, the chi-squared test).

#### Unsolicited adverse events:

Unsolicited adverse events will be coded with the MedDRA coding terminology. The intensity of adverse events will be graded according to section 7.1.7.

The number of adverse events and number of patients with at least one adverse event for each preferred term will be descriptively compared between treatment groups.

The occurrence of any grade 3 or higher adverse reaction probably, possibly or definitely related to the study vaccine within 28 days after vaccination will be compared between treatment groups.

The occurrence, relationship and intensity of *adverse events of special interest* at any time during the study will be separately listed and tabulated. The incidence of such AEs will be compared between treatment groups by means of the exact test of Fisher (or its normal approximation, the chi-squared test).

*Serious adverse events* will be listed separately. Each SAE will be described individually in detail. The number of subjects with at least one SAE will be compared between treatment groups by means of the exact test of Fisher (or its normal approximation, the chi-squared test).

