### The secondary objectives of the trial are:

- To assess safety of MVA-BN® (IMVAMUNE®) in subjects with atopic dermatitis compared to healthy subjects
- To assess reactogenicity of MVA-BN® (IMVAMUNE®) in subjects with atopic dermatitis compared to healthy subjects
- To assess the immune responses measured with the plaque reduction neutralization test (PRNT) and the Enzyme-Linked Immunospot (ELISPOT) assay induced to MVA-BN® (IMVAMUNE®) in subjects with diagnosed atopic dermatitis compared to healthy subjects. ELISPOT: Subgroup of 50 subjects from Group 1 (healthy) and 110 subjects from Group 2 (AD) with samples taken at each of the Visits 1, 2 and 4 collected at US sites. The first subjects enrolled into the study will be included in the subgroup until the numbers specified above are reached.

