## **4. Selection of subjects**

### **4.1 Recruitment procedure**

Volunteers will be recruited actively. Methods of recruitment mainly include Investigator databases and referrals from dermatological clinics and general practitioners specialized on dermatology. Recruitment strategies including paid advertisements, announcements and distribution of flyers will be evaluated.

In total, 560 individuals (260 subjects in the main study and then a further 100 healthy and 200 AD subjects in the extension phase) as defined in Section 4.2 will be enrolled. After signing the Informed Consent, subjects undergo screening procedures to check eligibility due to the following inclusion/exclusion criteria. In the event of a screen failure secondary to mild or limited acute illness or abnormal laboratory values the patient may be re-screened after resolution of the event. Re-screening may require only an additional blood draw or a complete re-screening evaluation, depending on the circumstances of and the time interval from the initial screening failure.

The Investigator will keep a log of subjects screened for the study, and provide the reason in case of exclusion.

Information about every patient entering the study will be provided to the contracted CRO.

Enrollment will be tracked to ensure that at least 50% of the subjects enrolled into Group 2 of the trial have active Atopic Dermatitis rather than history of Atopic Dermatitis. If it becomes apparent that less than 50% of group 2 have active AD then further enrollment of subjects with history of AD will be temporarily halted until the balance is once again achieved.

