### 16.4.4 Statistical Considerations

The primary objective of this protocol extension is to estimate the frequency of common and uncommon reactions in 300 vaccinia-naïve subjects with diagnosed atopic dermatitis. This sample size will allow the detection of 1 (one) unexpected adverse reaction in 100 (one hundred) subjects with 95% confidence, provided there is no background incidence of the respective adverse reaction.

The below table provides information on different scenarios for this assumption. The following sample sizes are needed to detect 1, 2 or 3 ADR with 95% certainty:

| Expected incidence of ADR | Number of subjects required to detect 1 ADR | Number of subjects required to detect 2 ADR | Number of subjects required to detect 3 ADR |
|----------------------------------|---------------------------------------------|---------------------------------------------|---------------------------------------------|
| 1:10                             | 28                                          | 46                                          | 61                                          |
| 1:50                             | 148                                         | 235                                         | 313                                         |
| 1:100                            | 298                                         | 473                                         | 627                                         |

---

 Calculated by solving the following equation for  $N$ :  $B(p_a; N, N_A - 1) = \beta$ , where  $B$  is the accumulated binomial distribution,  $N_A$  is the number of adverse events we wish to (be able to) detect and  $\beta = 0.05$ .

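### For rare safety events, section 9.4.3 names only a Fisher or chi-squared test, which neither estimates nor bounds an excess in subjects with atopic dermatitis

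*Protocol*

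**What the plan says.** Section 2 makes the safety objective comparative: "To assess safety of MVA-BN ® (IMVAMUNE ® ) in subjects with atopic dermatitis compared to healthy subjects". Appendix IV, section 16.4.4, adds an estimation objective: "The primary objective of this protocol extension is to estimate the frequency of common and uncommon reactions in 300 vaccinia-naïve subjects with diagnosed atopic dermatitis". It justifies the number as follows: "This sample size will allow the detection of 1 (one) unexpected adverse reaction in 100 (one hundred) subjects with 95% confidence". The same sentence attaches one condition to that claim: "provided there is no background incidence of the respective adverse reaction".

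Section 9.4.3 then gives the between-group methods. For serious adverse events: "The number of subjects with at least one SAE will be compared between treatment groups by means of the exact test of Fisher". For adverse events of special interest: "The incidence of such AEs will be compared between treatment groups by means of the exact test of Fisher". In both cases the chi-squared test is allowed as an approximation. The ECG paragraph uses the same test for normal or abnormal and for clinically significant ECGs. Related events of Grade 3 or higher are to be compared between groups, but no method is named.

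The section also plans descriptive output. Each serious adverse event is listed and described, special-interest events are listed and tabulated, and section 9.4.4 provides absolute and relative counts. In section 9, confidence intervals appear only for the seroconversion difference and the geometric mean titers. No significance level or sidedness is given for the safety tests.

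**The concern.** A test of no difference answers neither stated question. It does not estimate how often a reaction occurs in AD subjects, and it does not say how large an excess over healthy subjects the data still allow. When events are rare, it will nearly always be non-significant, whether or not AD subjects carry an added risk of about one percentage point.

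Section 1.4.2 notes that patients with atopic disorders are normally excluded from traditional smallpox vaccines, and section 9.4 foresees a safety analysis for a possible Emergency Use Authorization package. What a reader needs from about 330 AD subjects is an upper limit on the event rate and on the excess. The named inference supplies neither.

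**Working it through.** **Inputs.**
- AD group: 130 + 200 = 330 (section 4.1, Appendix V). The sizing in 16.4.4 uses 300.
- Healthy group: 130 + 100 = 230 (section 4.1, Appendix V).
- Reaction rate: 1% in AD, 0% in healthy. This is the 16.4.4 case, with its no-background condition carried over to the healthy group.
- Level: 5% two-sided is an assumption, because none is stated for safety.

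**Step 1. Reproduce the plan's own figure.** The formula in 16.4.4 asks for N such that P(no case) = 0.05. With p = 0.01 this is 0.99^N:
- N = 298: 0.0500
- N = 299: 0.0495

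The stated 298 agrees to within one subject. The probability of seeing at least one case is 1 − 0.99^300 = 95.1% with 300 subjects and 1 − 0.99^330 = 96.4% with 330. The sizing holds.

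**Step 2. How many cases the named test needs.** With 0 of 230 healthy subjects affected, x cases among 330 AD subjects give:

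| x | Fisher, two-sided p | Fisher, one-sided p | P(X ≥ x) at 1% |
|---|---|---|---|
| 3 | 0.27 | 0.20 | 0.642 |
| 6 | 0.086 | 0.041 | 0.116 |
| 7 | 0.045 | 0.024 | 0.050 |
| 8 | 0.024 | 0.014 | 0.019 |

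The expected number of cases is 330 × 0.01 = 3.3. Two-sided Fisher needs 7, so it is non-significant with probability 1 − 0.050 = 95.0%.

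**Step 3. Variants, still 1% against 0%.**

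| Variant | Cases needed | Non-significant |
|---|---|---|
| Fisher two-sided 5%, 330 vs 230 | 7 | 95.0% |
| Fisher one-sided 2.5%, 330 vs 230 | 7 | 95.0% |
| Fisher one-sided 5%, 330 vs 230 | 6 | 88.4% |
| Chi-squared uncorrected, 330 vs 230 | 6 | 88.4% |
| Chi-squared with continuity correction, 330 vs 230 | 8 | 98.1% |
| Fisher two-sided 5%, 300 vs 230 | 6 | 91.7% |

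**Step 4. Other rates (two-sided Fisher 5%, 330 vs 230).**

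| Healthy | AD | Non-significant |
|---|---|---|
| 0% | 2% | 51% |
| 0% | 3% | 13% |
| 1% | 2% | 92% |
| 1% | 3% | 71% |
| 1% | 4% | 44% |
| 2% | 5% | 58% |

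The weakness is greatest for excesses of one or two percentage points and fades as the excess grows.

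**Step 5. What an interval would say.** Exact (Clopper-Pearson) two-sided 95% limits for the AD group:
- 0 of 330: upper limit 1 − 0.025^(1/330) = 1.11%
- 3 of 330: 0.91%, interval 0.19% to 2.63%

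For 3 of 330 against 0 of 230, the difference is 0.91 points. A Newcombe 95% interval, used here only as an illustration, runs from −0.84 to 2.64 points. Fisher's p-value for the same data is 0.27. The interval shows that an excess of more than two points remains possible; the p-value does not.

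**The case against.** The strongest reply is that this is a matter of reporting. Intervals on adverse event rates are commonly left to the statistical analysis plan, which is not at hand, and nothing in 9.4.3 rules them out. That stands as far as it goes: a missing interval alone would be a weak point. What remains is that the protocol itself names the comparison method, and that method does not match its own estimation objective.

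Three stronger readings are tempting, and the documents do not support them.
- A reader might infer that the trial would overlook a 1-in-100 reaction about 95% of the time. It would not. Section 16.4.4 makes a one-group statement about seeing at least one case, the design meets it, and the case would appear in the planned counts or listings. What is missed is statistical significance between groups, for which the extension was never sized.
- A reader might infer that the sponsor intends to treat a non-significant result as proof of comparable safety. No passage says so, and no success rule for safety is set.
- A reader might extend the point to solicited reactions. Those were common in the pilot trial (fatigue in 33.3% of healthy subjects and 62.5% of those with a history of AD), and at these sample sizes a normal approximation gives about 90% power for 10% against 20%.

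It is also fair to say that relative counts already give point estimates, from which intervals can be derived. The frequency objective is therefore partly served, but without any stated precision.

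**Conclusion.** The point holds for rare outcomes: serious adverse events, special-interest events and clinically significant ECGs. The only inference named for comparing the groups would be non-significant about 88% to 98% of the time for a reaction at 1% in AD and 0% in healthy subjects (95% for two-sided Fisher; 92% with 300 AD subjects). This rests on an assumed 5% level and on all 330 and 230 planned subjects being analysed. The conclusion of low power survives every variant tried, but no single percentage is fixed by the protocol.

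This is a mismatch between method and objective, not an error in the sizing or a gap in safety surveillance. It is a cheap improvement.

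**What to change.** In 9.4.3, for serious adverse events, special-interest events, related events of Grade 3 or higher and clinically significant ECGs:
- Make the primary presentation the incidence per group with an exact 95% confidence interval, together with the AD-minus-healthy difference with an exact unconditional 95% confidence interval. Sections 9.1 and 9.4.2 already specify that type of method for seroconversion.
- Keep the Fisher p-values as supplementary.
- State that p > 0.05 is not evidence of comparable safety.

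No new data or visits are needed. The cost is a short text change and a few table columns. The downside is presentational: upper limits such as 1.1% for 0 of 330 or 2.6% for 3 of 330 look less reassuring than a non-significant p-value.
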